### Measurements

All measurements for primary and secondary endpoints will take place at baseline, post-intervention and 1 year follow-up. The Usual Care group will undergo an additional assessment point at the end of their delayed intervention. All groups will complete an additional assessment at 6 months follow-up involving the self-report questionnaires only. All assessments tools and procedures have established validity and reliability and are used widely in clinical research.

### Primary study endpoints

#### Sexual health

The IIEF will be utilised to assess sexual health across a variety of domains including erectile function, orgasmic function, sexual desire, intercourse satisfaction and overall satisfaction [41]. The Sexual Function scale of the EPIC is a prostate cancer specific tool which will be utilised to assess sexual function and satisfaction [42]. Sexual activity level will be assessed using the sexual domain of the QLQ-PR25 [43].

### Secondary study endpoints

Secondary endpoints include key factors associated with sexual health in men with prostate cancer.

#### Sexual self-confidence

The Short Form Psychological and Interpersonal Relationship Scale will be used to assess sexual self-confidence [44]. The Sexual Self-Efficacy Scale For Erectile Disorder will be applied to assess sexual self-efficacy [45].

#### Masculine self-esteem

The Masculine Self-Esteem Scale is designed specifically for use in men with prostate cancer and will be utilised to assess participant’s appraisal of their masculinity [46]. The Personal Attributes Questionnaire will evaluate masculinity [47].

#### Utilisation of sexual aids

A previously developed scale will be applied to assess whether participants have sought medical assistance for sexual dysfunction at any point before, during or after prostate cancer treatment [34,48]. All treatments will be documented and impact of these treatments rated.

#### Relationship satisfaction

The Dyadic Adjustment Scale will assess relationship satisfaction between participants and their partners [49].

#### Sexual supportive care needs

The level of need for help with sexual dysfunction will be assessed by the sexuality domain of the Supportive Care Needs Survey [50].

#### Quality of life

Health-related quality of life will be assessed using the Medical Outcomes Short Form 36 [51]. Quality of life will also be assessed using a prostate cancer specific tool, the EORTC QLQ-C30 and QLQ-PR25 questionnaires [52].

#### Urinary, bowel & hormonal issues

Adverse side effects specific to prostate cancer treatments will be assessed using the urinary function, bowel habits and hormonal function scales of the EPIC [42].

#### Psychological distress

The Brief Symptom Inventory-18 will be utilised to assess psychological distress across the following domains: anxiety, depression, somatisation and global distress severity [53]. Antidepressant use will also be recorded.

#### Fatigue

Cancer related fatigue will be assessed using the Functional Assessment of Chronic Illness Therapy-Fatigue questionnaire [54].

#### Body composition

Regional and whole body lean mass and fat mass will be derived from whole body dual-energy X-ray absorptiometry scans. Trunk adiposity, visceral fat and adipose indices will be assessed using standard procedures [55].

#### Body image

The Body Image Scale is a cancer-specific scale that will be used to assess participants’ perceptions of their appearance [56].

#### Physical function & physical activity levels

A series of standard tests will be used to assess physical function: 1) 400-m walk (aerobic capacity), 2) one repetition maximum in the leg press and chest press (muscular strength), 3) repeated chair rise (muscular power), 4) usual and fast pace 6-m walk (ambulation), and 5) backwards tandem 6-m walk (balance) [20,22,57]. Physical activity levels will be assessed objectively over a 7-day period using a validated, reliable tri-axial accelerometer activity monitor (ActiGraph GT3X+) [58]. Self-reported physical activity will also be assessed by the leisure score index from the Godin Leisure-Time Exercise Questionnaire [59].

#### Blood biomarkers

Blood samples will be collected and analysed commercially by accredited Australian National Association of Testing Authorities laboratories for testosterone, high sensitivity C-reactive protein (cardiovascular disease risk; also related to severity of penile vascular disease) and prostate specific antigen.

#### Exercise intervention

The exercise intervention involves a combination of aerobic and resistance exercise performed during 3 sessions per week for 6 months. The program will be supervised by accredited exercise physiologists in various exercise clinics in Western Australia, Queensland and New South Wales. The exercise sessions will be conducted in small groups of up to 10–12 participants exercising in pairs or under direct supervision to ensure correct technique and minimise the risk for injury. The exercise program is designed to provide optimal stimulus to the cardiorespiratory and neuromuscular systems while maximising safety, compliance and retention. Specifically, the aerobic exercise component will include 20 to 30 minutes of moderate to vigorous intensity cardiovascular exercise (~60-85% of estimated maximum heart rate) using a variety of modes such as walking or jogging on a treadmill, cycling or rowing on a stationary ergometer or exercising on an elliptical or cross trainer machine. Participants will be encouraged to undertake additional home-based aerobic exercise with the goal of achieving a total of at least 150 minutes of moderate intensity aerobic exercise each week. The resistance exercise component will involve 6–8 exercises that target the major upper and lower body muscle groups. Intensity will be manipulated from 6–12 repetition maximum (RM; i.e. the maximal weight that can be lifted 6 to 12 times which is equivalent to ~60-85% of 1RM) using 1–4 sets per exercise. To ensure the progressive nature of the training program, participants will be encouraged to work past the specific RM prescribed. The resistance will be increased by a 5-10% increment for the next set or training session if the subject is able to perform more repetitions than the RM specified during a set. Each session will commence with a 10-minute warm-up comprised of low-level aerobic activities as well as stretching and conclude with a 5-minute cool-down period of stretching activities. Exercise prescription will be progressive and modified according to individual response. In order to reduce the possibility of boredom and over-reaching, the exercise program will be periodised by cycling emphasis on intensity and volume. The exercise intervention has been designed in accordance with international guidelines [60,61]. Furthermore, we have used this exercise prescription effectively in previous trials involving men with prostate cancer and have reported significant improvements in libido, quality of life, lean muscle mass, fatigue, aerobic capacity, muscular strength, physical function and C-reactive protein [20,22,23,26].

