### Participants

Two hundred and forty men (80 subjects per arm) treated for prostate cancer will be recruited by invitation from their attending specialist (oncologist/urologist). Participants will be recruited in Perth, Western Australia; Brisbane, Queensland; Central and North Coasts of New South Wales. Inclusion criteria are: 1) concern about sexual health as assessed by an International Index of Erectile Functioning (IIEF) overall satisfaction score < 8 (i.e. moderately-very dissatisfied) [41] and/or Expanded Prostate Cancer Index Composite (EPIC) sexual bother score > 8 (i.e. small-big problem) [42]; 2) prior/current treatment for prostate cancer including prostatectomy, radiotherapy or ADT; and 3) physician consent. Exclusion criteria are: 1) non-nerve sparing prostatectomy; 2) > 6 months since prostatectomy or completion of radiotherapy or ADT; 3) incontinence defined as requiring the use of > 1 pad in a 24-hour period; 4) already performing regular exercise defined as undertaking structured aerobic or resistance training two or more times per week within the past 3 months; 5) acute illness or any musculoskeletal, cardiovascular or neurological disorder that could inhibit exercise or put participants at risk from exercising; and 6) unable to read and speak English. Eligible subjects will undertake a series of familiarisation sessions and baseline measurements prior to randomisation (Figure 2). The protocol has been approved (ID: 10643 [name]) for all participating centres by the Edith Cowan University Human Research Ethics Committee and all participants will provide written informed consent.

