### Randomisation

Subjects will be randomly allocated in a ratio of 1:1:1 to the three study arms, subject to maintaining approximate balance regarding stratification for: 1) age (<60 years≥); 2) current sexual activity level (no/minor-moderate) as assessed by the European Organisation for Research and Treatment of Cancer (EORTC) prostate cancer specific questionnaire (QLQ-PR25) sexual activity score [43]; 3) previous prostatectomy (yes/no); 4) previous radiotherapy (yes/no); and 5) previous/current ADT (yes/no). A research methods consultant with no patient contact will be responsible for randomisation which will be performed in Statistical Analysis System using the Pocock-Simon minimisation algorithm.

The inclusion and exclusion criteria and stratification procedures have been designed to control for the major factors that may influence either baseline values and/or the potential for change in sexual health throughout the intervention (e.g. treatment type, time since treatment, level of sexual health both pre-treatment and at baseline, age, potential for recovery of function, incontinence). Furthermore, in addition to clinically relevant covariates, the main factors that could potentially confound the results will be assessed and adjusted for (e.g. utilisation of sexual aids [pre-treatment, post-treatment and throughout the study period], relationship status and satisfaction, any additional cancer treatment during the study period, side effects and co-morbidities influencing sexual health).

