
#### Exercise and psychosexual intervention

Participants receiving the combined exercise and psychosexual support and self-management will complete the exercise intervention described above as well as a brief psychosexual self-management component that addresses psychological and sexual well-being. A low intensity psychological care approach will be utilised in order to maximise uptake and accessibility (i.e. facilitates translation) [62]. Specifically, at baseline, participants will receive a face to face brief psychosexual self-management session with their exercise physiologist that addresses: stress management; problem solving coping for treatment challenges; and goal setting for sexual rehabilitation. These sessions will be audiotaped with 15% reviewed to ensure adherence to the intervention protocol. The psychosexual self-management intervention will apply cognitive behavioural strategies; will utilise an adult learning approach in which men self-select goals to focus on; and will encourage self-management [63]. To support self-management men will receive a psychosexual kit that includes a published self-help book for men with prostate cancer and their partners [64]; study specific tip sheets about treatments for erectile dysfunction and goal setting for sexual rehabilitation; a progress journal-diary; and audio resources for stress management. The intervention delivered by the exercise physiologist will be manualised and based on existing materials already developed and trialled by the team [31,48]. The exercise physiologists will receive extensive training in how to deliver the intervention and continued supervision. Treatment fidelity will be managed consistent with National Institute of Health guidelines [65]. This pragmatic approach has been adopted based on the fact that men are low help-seekers and incorporating strategies that are linked to masculine ideals (i.e. exercising linked to physical strength, self-management as self-reliance, peer support offered through exercising in a group or ‘team’ of men rather than a traditional support group setting) may be more accepted by men and effective [37-39].

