#### Statistical analysis

Data from our previous 3-month study in prostate cancer patients indicates that the standard deviation for change in our primary outcome of sexual health equates to ~22 points on the QLQ-PR25 sexual activity domain [26]. We observed the mean change after the intervention to differ between exercise and usual care groups by ~11 points [26]. There is no available evidence comparing changes in sexual health between exercise and psychosexual interventions. However, data from previous psychosexual interventions in prostate cancer patients indicates changes of a moderate standardised effect (*d* = 0.5) in sexual health following the psycho-educational interventions [32,33]. We have based sample size calculations on the assumption that there will be an additive effect of exercise and psychosexual therapies. A priori, 64 participants per group will be required to achieve 80% power at an alpha level of 0.05 (two tailed), and to demonstrate a difference between the three groups in sexual health at the end of the intervention. Previous experience in exercise and psychosexual therapy trials indicates an attrition rate of up to 20% over the intervention period. Therefore, to adequately ensure that we have sufficient participant numbers at the end of the intervention, 240 participants will be randomised to the study arms. A sample size of 240 will also provide us with sufficient power to detect a moderate standardised effect (*d* = 0.5) in our secondary outcomes. Based on previous experience we anticipate a further attrition rate of up to 20% over the follow-up period. Therefore, the sample size will provide 87% statistical power to detect differences between the Exercise group and the Exercise + Psychosexual group at follow-up (*d* = 0.5; n = 77 per group as the usual care group will be split between the two interventions for the prospective cohort study component of this project).

Data will be analysed using an intention-to-treat approach with maximum likelihood imputation of missing values. Analyses will include standard descriptive statistics, Student’s t-tests, chi-square, correlation and regression, and two way (group × time) repeated measures ANOVA (or ANCOVA as appropriate) to examine differences between groups over time. Clinically relevant covariates will be included in analyses. All tests will be two-tailed and an alpha level of 0.05 will be applied as the criterion for statistical significance.

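### Group-based exercise at several sites: site is left out of the minimisation, and the sample size and named analyses make no allowance for correlation within exercise groups

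*Protocol article*

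**What the plan says.** Recruitment covers several regions (Protocol article, Participants): "Participants will be recruited in Perth, Western Australia; Brisbane, Queensland; Central and North Coasts of New South Wales". Under Exercise intervention, training takes place three times a week for 6 months at clinics in three states, supervised by exercise physiologists: "The exercise sessions will be conducted in small groups of up to 10–12 participants". Under Exercise and psychosexual intervention, the psychosexual session is delivered by the man's exercise physiologist, and the rationale counts on "peer support offered through exercising in a group or ‘team’ of men". Usual Care has no such group contact during the first 6 months.

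Under Randomisation, men are allocated individually: "Subjects will be randomly allocated in a ratio of 1:1:1 to the three study arms". Pocock-Simon minimisation is used on age, sexual activity level, prostatectomy, radiotherapy and ADT. Site is not in that list, nor among the confounders given there as examples for adjustment.

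Under Statistical analysis, the sample size is stated as "64 participants per group will be required to achieve 80% power at an alpha level of 0.05 (two tailed", raised to 240 in total for attrition. The named analyses are t-tests, chi-square, correlation and regression, and a group-by-time repeated measures ANOVA or ANCOVA with unspecified clinically relevant covariates. No term for site, exercise group or physiologist is named.

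**The concern.** Men who train together for 6 months, or under one physiologist, may end with more similar outcomes than men drawn at random. The article's own rationale makes this plausible, because it treats the group as a source of benefit. Usual Care men share no such exposure before month 6, so any clustering sits in the exercise arms only. An analysis that treats every man as independent would then understate the standard error of Exercise versus Usual Care, and the stated power would be too high.

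Site is a different matter. Clinics can differ in patient mix and in delivery. With site absent from the minimisation, the arms may differ in their share of each clinic by chance. With site absent from the model, variation between clinics stays in the residual error.

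**Working it through.** **Inputs from the Statistical analysis section**
- SD: "the standard deviation for change in our primary outcome of sexual health equates to ~22 points on the QLQ-PR25 sexual activity domain".
- Difference: "We observed the mean change after the intervention to differ between exercise and usual care groups by ~11 points".
- Attrition: "indicates an attrition rate of up to 20% over the intervention period".
- Two-sided alpha 0.05, 80% power.

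**Assumptions, not in the article**
- Stable exercise groups of m = 11, the middle of the 10–12 ceiling.
- ICC of 0.01, 0.02 or 0.05 for the change score.

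**Reproducing the plan's figures**
- d = 11/22 = 0.5. The two-sample t-test needs 63.8, so 64 per group (power 80.1%).
- 64/0.8 = 80 per arm, and 3 × 80 = 240.
- Follow-up: 240 × 0.8 × 0.8 / 2 = 76.8, so 77 per group, with power 86.9% (stated 87%).

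All three reproduce with independent men, so the allowance for clustering is nil.

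**Effect of clustering within exercise groups**
- Design effect in a clustered arm: DE = 1 + (m − 1) × ICC = 1 + 10 × ICC = 1.1 / 1.2 / 1.5.
- Variance inflation of the difference: V = (1 + DE)/2 if one arm is clustered, and V = DE if both are, each in its own groups.
- Type I error of the unadjusted test: 2 × [1 − Φ(1.96/√V)].
- True power: t-test with d = 0.5 and effective n = 64/V per group.

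| Comparison | ICC | V | 1.96/√V | Type I error | 64/V | Power |
|---|---|---|---|---|---|---|
| Exercise vs Usual Care | 0.01 | 1.05 | 1.913 | 5.6% | 61.0 | 78% |
| | 0.02 | 1.10 | 1.869 | 6.2% | 58.2 | 76% |
| | 0.05 | 1.25 | 1.753 | 8.0% | 51.2 | 71% |
| Exercise + Psychosexual vs Exercise, only if trained in separate groups | 0.01 | 1.10 | 1.869 | 6.2% | 58.2 | 76% |
| | 0.02 | 1.20 | 1.789 | 7.4% | 53.3 | 73% |
| | 0.05 | 1.50 | 1.600 | 11% | 42.7 | 63% |

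The follow-up comparison uses 77/V per group, with both arms clustered in separate groups. The stated 87% becomes 84 / 80 / 71%.

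A simulation of the unadjusted t-test (20,000 runs, 64 per arm, groups of 10 or 12) agrees. For Exercise versus Usual Care at ICC 0.05 it rejected a true null in 7.5–8.1% of runs.

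**Sensitivity to group size.** With m = 6 (also assumed), DE = 1 + 5 × ICC and V = 1.025 / 1.05 / 1.125. Type I error for Exercise versus Usual Care is then 5.3 / 5.6 / 6.5%. At ICC = 0 nothing changes.

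**Effect of omitting site.** These simulations assume three equal sites and simple random allocation.
- With a site ICC of 0.05 and site ignored, the t-test rejected a true null in 5.1% of 5,000 runs, so there was no inflation.
- The difference between two arms in one site's share had a median of 5 percentage points and a 95th percentile of 15. It was 10 points or more in about 20% of 20,000 allocations.

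**The case against.** The strongest reply is that the cluster structure is assumed. The 10–12 figure is a ceiling on session size, not a description of closed cohorts. Nothing says that a man keeps the same group for 6 months. Prescriptions are individualised, home exercise is encouraged, and the psychosexual element is one manualised session. This stands: the size of the effect is conditional, and at ICC 0.01–0.02 it is small.

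A second reply is that the covariate clause is open, ANCOVA and regression are allowed, and an analysis plan not shown could add site or a random effect. This also stands for the model, so the absence of those terms is not in itself an error. It does not reach the minimisation list or the sample size, which this article fixes. Nor could a later plan recover group membership that was never recorded.

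A reader might infer that omitting site makes the standard errors too small, or confounds arm with clinic. Neither follows. Men are randomised individually, so chance imbalance by site is already covered by the test, as the 5.1% result shows. A reader might also take the 11% type I error and 63% power as the expected case. They need both ICC 0.05 and single-arm groups, and the article states neither. If the groups mix the two exercise arms, the effect on that comparison is smaller or absent.

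**Conclusion.** The point holds in a limited form, as a cheap improvement and not as a flaw that undermines the trial. Omitting site costs precision and leaves balance across clinics to chance; it does not raise type I error. Separately, the sample size and the named analyses allow nothing for correlation within exercise group or physiologist, although the intervention is delivered in groups and counts on peer support. For Exercise versus Usual Care the consequence runs from negligible at ICC 0.01 to material at 0.05 (8.0% type I error, 71% power), given stable groups of 11. Any effect on the comparison between the two exercise arms also depends on their training in separate groups.

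**What to change.** - Add site, defined as recruiting region or clinic, as a sixth minimisation factor and as a fixed effect in the primary model.
- Record exercise group and physiologist for each man, and state whether groups are stable and whether they mix the two exercise arms.
- Fit a partially nested mixed model with a random intercept for exercise group or physiologist in the exercise arms only. Use a small-sample degrees-of-freedom correction, since 64/11 gives only about six groups per arm and the variance component will be poorly estimated.
- Restate the 80% and 87% power figures over a stated ICC range, without enrolling more men.

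The cost is a small change to the minimisation program, one extra identifier on the record form, slightly wider intervals and a less favourable stated power. The minimisation factor and the identifiers help only if they are in place early.

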
#### Exercise and psychosexual intervention

Participants receiving the combined exercise and psychosexual support and self-management will complete the exercise intervention described above as well as a brief psychosexual self-management component that addresses psychological and sexual well-being. A low intensity psychological care approach will be utilised in order to maximise uptake and accessibility (i.e. facilitates translation) [62]. Specifically, at baseline, participants will receive a face to face brief psychosexual self-management session with their exercise physiologist that addresses: stress management; problem solving coping for treatment challenges; and goal setting for sexual rehabilitation. These sessions will be audiotaped with 15% reviewed to ensure adherence to the intervention protocol. The psychosexual self-management intervention will apply cognitive behavioural strategies; will utilise an adult learning approach in which men self-select goals to focus on; and will encourage self-management [63]. To support self-management men will receive a psychosexual kit that includes a published self-help book for men with prostate cancer and their partners [64]; study specific tip sheets about treatments for erectile dysfunction and goal setting for sexual rehabilitation; a progress journal-diary; and audio resources for stress management. The intervention delivered by the exercise physiologist will be manualised and based on existing materials already developed and trialled by the team [31,48]. The exercise physiologists will receive extensive training in how to deliver the intervention and continued supervision. Treatment fidelity will be managed consistent with National Institute of Health guidelines [65]. This pragmatic approach has been adopted based on the fact that men are low help-seekers and incorporating strategies that are linked to masculine ideals (i.e. exercising linked to physical strength, self-management as self-reliance, peer support offered through exercising in a group or ‘team’ of men rather than a traditional support group setting) may be more accepted by men and effective [37-39].

